#### Dropout exclusion criteria

Each participant’s completion status will be monitored. In case of discontinuation, the reason for the discontinuation will be recorded. Cases in which the trial can be discontinued are as follows: 

The investigators discover that the participant does not meet the inclusion or exclusion criteria.The participant experiences any serious adverse events (AEs) or adverse events that make continuation in the trial challenging.The participant or legal representative requests to discontinue the trial owing to unsatisfactory therapeutic effects.The compliance of each participant is < 80%.The investigators or participants violate the study protocol.The participant withdraws consent to participate in the trial.The participant is lost to follow-up.The participant receives any treatment that may affect the study results without the investigator’s approval.Participants deemed incapable of continuing the trial by the investigators.

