### Sample size

In our previous study, the mean changes in the O-SCORAD score for 4 weeks were 9.2 ± 3.73 and 7.2 ± 3.91 in the BMA-AD and IDA-AD groups, respectively. Based on these results, we will conservatively evaluate the changes for 4 weeks in the BMA and sham devices. The number of participants required for this study was calculated as follows:$${n}_{1}=\frac{{2({Z}_{\alpha/2}+{Z}_{\beta})}^{2}{\sigma}^{2}}{{\left(\mu1-{\mu}_{2}\right)}^{2}}=64$$

The required sample size was determined to be 64 cases per group (‘experimental group’ and ‘control group’).$$N=\frac{{n}_{1}}{1-r}\cong92$$

Assuming a 30% drop out rate of participants at follow-up, we calculated the sample size to be 92 cases for each group and a total of 184 participants for both groups.

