#### General principles

The safety and full analysis sets (FAS) of this trial will include all the participants who received any intervention at least once after randomization. The per-protocol set will only include participants in the FAS who completed the entire trial without protocol violations. The FAS is primarily used for outcome analysis, although additional outcome analyses of the per-protocol set may be performed. The safety set will be used for safety assessments, including the primary outcome of the trial. Missing values will be handled using the last observation carried-forward method.

Statistical analyses will be performed using SAS (SAS Institute Inc., Cary, NC, USA) or SPSS (IBM Corp., Armonk, NY, USA) softwares for Windows. Statistical significance is set at *p* < 0.025 for a one-tailed test and *p* < 0.05 for a two-tailed test.

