#### Economic outcomes analysis

The QALYs will be calculated using the Area Under the Curve (AUC) method. Treatment costs will be estimated by combining the frequency of each treatment and their unit costs. The economic evaluation will primarily follow the Intention-to-Treat (ITT) principle, which includes all randomized participants, regardless of adherence to the treatment protocol, to assess the effectiveness of the treatments. A secondary analysis will be performed based on the Per-Protocol (PP) principle to evaluate the sensitivity of results to missing data. For missing data in the ITT analysis, the missing data mechanism will be primarily examined using missing diagnosis method, and appropriate imputation method will be applied for building up ITT data before proceeding the analysis. The analysis period will be 8 weeks (the total follow-up period). If additional extrapolation is required, regression models or decision analysis models will be used to estimate costs and effects beyond the follow-up period. After the clinical trial period, the total analysis duration will use the 2024 South Korean currency (KRW) for cost calculations, and a 5% discount rate will be applied, in accordance with the Health Insurance Review and Assessment Service (HIRA) guidelines for cost-effectiveness evaluations. The analysis will be conducted from a societal perspective. In the base-case analysis, representative values (such as mean values) for parameters will be used, while probabilistic sensitivity analysis will be performed using all possible distributions and representative values for the estimated parameters. The results will be presented in tables, including Incremental Cost-Effectiveness Ratios (ICER), Cost-Effectiveness Planes (CEP), Cost-Effectiveness Acceptability Curves (CEAC), and Information Curve values. Statistical analysis for the economic evaluation will be conducted using Stata (MP 16.1) and R (4.3.2), and modeling for extrapolation will be performed using TreeAge Pro(Healthcare version 2023).

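### The economic evaluation uses a per-protocol analysis to test sensitivity to missing data, but that analysis changes the population and leaves the missing-data assumption untested

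*Protocol article*

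**What the plan says.** All of this comes from the protocol article.

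- **Economic outcomes analysis, main population:** "The economic evaluation will primarily follow the Intention-to-Treat (ITT) principle, which includes all randomized participants, regardless of adherence to the treatment protocol".
- **Same section, missing data in that population:** the mechanism is examined first, and then an "appropriate imputation method will be applied for building up ITT data before proceeding the analysis". The method is not named.
- **Same section, sensitivity to missing data:** "A secondary analysis will be performed based on the Per-Protocol (PP) principle to evaluate the sensitivity of results to missing data".
- **Same section, other sensitivity work:** "probabilistic sensitivity analysis will be performed using all possible distributions and representative values for the estimated parameters".
- **General principles:** "The per-protocol set will only include participants in the FAS who completed the entire trial without protocol violations". The full analysis set (FAS) is itself limited to participants who received at least one intervention after randomization.
- **Sample size:** "Assuming a 30% drop out rate of participants at follow-up", which takes 64 per group to 92.
- **Dropout exclusion criteria:** grounds for discontinuation include adverse events, a request to stop because the effect is unsatisfactory, and low adherence ("The compliance of each participant is < 80" percent).

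**The concern.** A missing-data sensitivity analysis should keep the question and the population fixed and change what is assumed about the values nobody observed. The per-protocol analysis does the reverse. It moves to a smaller, selected population and assumes nothing new about the missing values.

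Two misreadings follow. If the per-protocol and imputed intention-to-treat results agree, the report may say that the cost-effectiveness result is robust to missing data when the assumption behind the imputation was never varied. If they disagree, nobody can say whether missing data or protocol adherence is the cause.

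Several listed reasons for discontinuation relate to how the participant is doing, so missingness that depends on outcome is plausible. The Discussion presents the economic assessment as support for broader coverage, so a robustness statement would carry weight.

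**Working it through.** **1. The plan's own figure.** From Sample size: 64/(1 − 0.30) = 91.4, rounded up to 92 per group and 184 in total. This reproduces. The 64 is taken as given, because nothing below depends on how it was reached.

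**2. How many leave the per-protocol set.** At the 30% allowance, 0.30 × 184 = 55.2. If exactly 64 per group remain, 184 − 2 × 64 = 56. The per-protocol set then holds at most about 128 or 129 of 184 (70%), and fewer once violators are removed.

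**3. The two analyses side by side.**

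| | Main economic analysis | Per-protocol |
|---|---|---|
| Randomized, never treated | included | excluded |
| Non-completers | included, imputed | excluded |
| Completers with violations | included | excluded |
| Assumption about unobserved values | that of the chosen imputation | no alternative stated |

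The first and third rows concern treatment received and adherence. Only the second is mainly about missing data. A contrast between the columns mixes all three.

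**4. What a completers-only difference leaves out.** Let r be an arm's non-completion rate and g the mean utility of its non-completers minus that of its completers. The arm mean in everyone is the completers' mean plus r × g. The difference between arms in everyone is therefore the completers' difference plus (r1·g1 − r0·g0), with 1 for BMA and 0 for sham. The g values are unobserved and not in the document. Taking r = 0.30 in both arms and assumed values of g:

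- g = −0.02 in both arms: 0.30 × (−0.02) − 0.30 × (−0.02) = 0
- g = −0.02 (BMA), 0 (sham): 0.30 × (−0.02) − 0 = −0.006
- g = −0.05 (BMA), −0.02 (sham): −0.015 + 0.006 = −0.009

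Against an assumed utility gain of 0.03, these are 0%, 20% and 30%. Over the stated 8-week horizon, the last two are at most 0.006 × 8/52 = 0.0009 and 0.009 × 8/52 = 0.0014 QALY. They show the mechanism and do not estimate this trial's bias.

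**5. Can both results be wrong together?** A simulation used assumed settings: 92 per arm, 30% missing, a true standardized difference of 0, a covariate correlated 0.5 with the outcome, regression imputation on that covariate within arm, and 2,000 runs.

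| Missingness | Completers only | Imputed |
|---|---|---|
| Completely at random | 0.00 SD | 0.00 SD |
| Poor outcomes more often missing, both arms alike | 0.00 SD | 0.00 SD |
| Poor outcomes more often missing, BMA arm only | 0.25 SD | 0.20 SD |

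In the last row the two results lie close together and both are wrong, so their agreement would reassure falsely. The simulation compares completers with imputed data. It does not model the extra selection on violations.

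**6. Does another stated analysis fill the gap?** The probabilistic sensitivity analysis addresses parameter uncertainty. The mechanism check belongs to the main analysis, and observed data alone cannot rule out dependence on unobserved values. The article names no analysis that varies the assumption about the missing values.

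**The case against.** The strongest defence is that missing data are taken seriously. The main economic analysis covers everyone randomized, with a mechanism check and imputation. An analysis plan exists but is not shown, and details of imputation models are normally left to it. That stands, and the unnamed imputation method is not criticized here. But the purpose given to the per-protocol analysis is stated in the article, and a fuller plan that follows this sentence inherits the problem.

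It can also be said that the economic section speaks of a per-protocol principle without restating the definition in General principles. That is true, but it offers no other definition, and any usual one conditions on adherence.

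A reader might infer stronger things that the document does not support:

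- **That the plan assumes data are missing at random.** It does not say so. The point holds whatever imputation is chosen, because per-protocol does not test that method's assumption.
- **That per-protocol drops everyone with missing data.** It drops non-completers and violators. A completer can still lack EQ-5D or cost items.
- **That the comparison is worthless.** It does show whether the result depends on the excluded participants. It is a weak and confounded check, not an empty one.
- **That 20% to 30% of the benefit is at stake.** Those figures rest wholly on assumed utilities, and the same formula gives zero when rates and gaps are equal in both arms.
- **That 30% of economic data will be missing.** The figure is a dropout allowance for sample size.

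**Conclusion.** The point holds as a mismatch between a stated method and its stated purpose. The per-protocol analysis cannot separate missingness from adherence, and its agreement with the intention-to-treat result does not establish robustness to missing data. This rests on reading per-protocol as General principles defines it. The shared-bias argument also requires missingness to depend on unobserved outcomes differently by arm, which is possible here but not shown.

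The size of any effect on the cost-effectiveness ratio cannot be derived from the document, which gives no expected utilities, costs or rate of missing EQ-5D data. The reach is limited: the economic evaluation is not the primary outcome, its base case remains intention-to-treat with imputation, and the O-SCORAD result is untouched. The wording should be changed, but the trial's main conclusion does not depend on it.

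**What to change.** In Economic outcomes analysis, describe the per-protocol analysis as an adherence analysis and remove the missing-data purpose from it. Then add one sentence: sensitivity to missing data will be examined in all randomized participants by repeating the imputation of costs and QALYs under changed assumptions about the missing values, and the report will give the shift at which the cost-effectiveness conclusion changes. Arm-specific delta shifts applied to the imputed values are one suitable way. The range of shifts and the imputation model can sit in the analysis plan.

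The cost is a sentence or two of text and a little extra programming. No new data, visits or participants are needed.

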## Discussion

BMA was developed using biodegradable hyaluronic acid microneedle technology to mitigate the side effectsof traditional metal needle acupuncture and enhance therapeutic efficacy. Conventional IDA ismade of metal tacks for continuous needle stimulation, which can cause side effects such as foreign body sensation, skin erythema, oozing, and itching in individuals with metal allergies. To eliminate these side effects, we developed BMA using hyaluronic acid, which has been proven to be safe as a biodegradable alternative to traditional metal materials.

AD is one of a group of recurrent chronic inflammatory skin diseases. It usually begins in childhood and persists into adulthood, though it can rarely develop in middle or old age. Most individuals with AD have underlying allergic asthma, allergic rhino conjunctivitis, food allergies, and other type 1 hypersensitivity reactions [1–3, 5, 8].

The treatment of AD depends on various factors, including the clinical stage (mild, moderate, or severe), affected body surface area, patient age, comorbidities, medications, pruritus severity, and quality of life impairment. Currently, no definitive cure exists [1, 2, 8]. The goal of AD treatment is to relieve symptoms, prevent exacerbations through early intervention, reduce relapses, and ultimately control disease progression to enable patients to engage in normal social activities without discomfort [1–3, 5, 8]. Various medications, including antihistamines, corticosteroids, and immunosuppressants, are used to alleviate AD symptoms; however, due to concerns regarding side effects and resistance with long-term use, there is a need for new therapeutic approaches [4, 8].

The authors have already conducted an exploratory investigator trial to evaluate the efficacy and safety of BMA versus IDA in AD. Although the BMA group demonstrated greater improvement in AD symptoms than the control group, statistical significance was not achieved due to the small sample size (*n* = 30). Dermal allergic adverse events were observed in the IDA group, whereas no adverse events were reported in the BMA group [9].

Acupuncture has already been reported in animal and human clinical trials to alleviate itching in dermatological conditions and improve AD symptoms, making it an increasingly important complementary and alternative treatment for dermatological conditions [6, 8, 18–20].

The authors propose a prospective, multicenter, randomized controlled trial (RCT)to evaluate the efficacy, safety, and cost-effectiveness of BMA in patients with moderate or milder AD. The O-SCORAD score will be adopted as the primary outcome measure, while EASI, VAS, POEM, and DLQI scores will serve as secondary outcome measures to enhance the reliability of the results. Additionally, safety, economic evaluation, and gut microbiome analysis will be conducted.

A key limitation of this study protocol is the 5-week evaluation period, which lacks long-term follow-up.While the study can assess short-term improvement following BMA treatment, it remains unclear whether the benefits persist over time. A key strength of this study protocol is that it is the first to evaluate the efficacy, safety, and cost-effectiveness of BMA for managing atopic dermatitis symptoms.

In summary, this multicenter, randomized, sham BMA–controlled study will assess the clinical efficacy and safety of BMA in managing symptoms of moderate or milder AD.

The demand for Korean medicine (KM) therapies in the management and treatment of AD symptoms is increasing. Although the authors developed BMA, there is currently insufficient evidence to support its efficacy and safety in AD treatment. Therefore, a high-quality, multicenter, well-designed RCT is necessary to provide further evidence. This RCT aims to provide evidence that BMA safely improves AD symptoms in patients with sensitive skin while simultaneously assessing its economic feasibility to support broader coverage.

## Data Availability

The data that support the findings of this study are available on request from the corresponding author. The data are not publicly available due to privacy or ethical restrictions.

## Abbreviations

AD: Atopic dermatitis
BMA: Biodegradable microneedle acupuncture
IDA: Intradermal acupuncture
O-SCORAD: Objective-SCORing Atopic Dermatitis
AST: Aspartate transaminase
ALT: Alanine transaminase
KMD: Korean medicine doctor
VAS: Visual analog scale
EASI: Eczema Area and Severity Index
DLQI: Dermatology Life Quality Index
POEM: Patient-Oriented Eczema Measure
eCRF: Electronic Case Report Form
AE: Adverse event
FAS: Full analysis set
QoL: Quality of life
KM: Korean medicine
